## Methods

### Study design

This study will be a 12-month, community-based, two-arm randomised controlled trial in women with BCa undergoing AC comparing (i) the ability of ExCMR versus resting echocardiography to predict patients who will become functionally disabled following AC; and (ii) the relative effectiveness of a 12-month supervised and structured multi-component exercise program to usual care for preventing functional disability following AC. A total of 100 women with BCa aged 40–75 years who are scheduled to undergo AC will be recruited and randomly allocated to either a 12-month multi-component exercise program (ET, *n* = 50) or a usual care control group (UC, n = 50). All assessments will be performed at the Baker Heart and Diabetes Institute (Melbourne, Victoria, Australia) at baseline (no more than 2-weeks following the commencement of AC), 4-months (~ 3 weeks following the completion of AC) and 12-months from the commencement of AC. A flow diagram of the study protocol is shown in Fig. 1. Where possible, all baseline assessments will be conducted prior to the commencement of AC, however this may not always be possible due to the short time frame between patients being informed of the decision to undergo AC and its commencement. This trial has been approved by the Alfred Hospital Human Research Ethics Committee (Project No: 305/17), is registered with the Australian and New Zealand Clinical Trials Registry (ACTRN12617001408370) and is funded by the World Cancer Research Fund International (Grant IIG_2019_1948).

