### Randomisation and blinding

Following baseline testing, each participant will be randomly allocated (1:1 ratio) to the intervention or control group by an independent researcher using a computer-generated, random number sequence with the outcome communicated via telephone. Stratified block randomisation will be used, with participants stratified by age (< 60 or ≥ 60 years) and human epidermal growth factor receptor 2 (HER2) status (positive or negative), with block sizes alternating between two and four participants. Participants, care providers and outcome assessors will not be blinded to group allocation. However, the quantification of all cardiac imaging (echocardiography and cardiac magnetic resonance imaging, CMR) will be performed by researchers blinded to subject identity. Furthermore, outcome assessors will be blinded to pre-chemotherapy values for all assessments.

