##### Aerobic ET

During phase 2, participants will complete four sessions per week of aerobic training. The aerobic training program completed during phase 2 will consist of four session types: maximal steady state, endurance, interval and recovery sessions (outlined in Table 1 and Fig. 2) that alternate in a bi-weekly cycle similar to previous work in middle-aged adults shown to improve fitness and cardiovascular function [47]. In the first week, participants will complete two tempo sessions, one endurance session, and one interval session. In the alternate week, participants will complete one tempo, and two interval sessions that are interspersed with a recovery session. Tempo sessions will consist of 35 min at the %HRR corresponding to VT ± 10 beats/min as measured from the follow-up CPET at the 4-month testing visit. Endurance sessions will begin with 40-min at the %HHR 10–20 beats/min below VT, and progress by 5-min every fortnight until participants are completing a total duration of 60-min. The interval sessions will be identical to those completed at the end of Phase 1 of the program (4-min intervals at 85–95% HR_peak_). During weeks that incorporate two interval sessions, these sessions will be interspersed with a recovery session consisting of 30-min at an intensity 20–30 beats/min below %HRR at VT.

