### Primary and secondary outcome measures

The primary outcome for this study will be the prevalence of functional disability (defined as VO_2_peak ≤ 18.0 mL/kg/min) measured via CPET at 12 months. The predictive ability of standard-of-care versus novel cardiac reserve measures will be addressed by comparing LVEF assessed via 3-dimensional (3D) echocardiography to cardiac reserve assessed via exCMR. For the purposes of this study, impaired cardiac reserve will be defined as a < two-fold increase in Qc from rest to peak exercise [33]. Impaired LVEF will be defined as a LVEF < 53% which is in line with current cardio-oncology guidelines [14, 15, 17].

Secondary outcomes will include changes in cardiopulmonary fitness and cardiac reserve, along with indices of resting cardiac structure and function, vascular stiffness, biochemical and blood-based markers of cardiovascular function, total- and regional body composition, bone mineral density of the lumbar spine and femoral neck, muscle strength, physical function, habitual physical activity, cognitive function, and multidimensional quality of life.

Additional exploratory outcomes will include the association between changes in cardiopulmonary fitness with indices of cardiac (cardiac reserve) versus non-cardiac factors (central vascular stiffness, haemoglobin concentration, lower body lean body mass, skeletal muscle composition of the thigh). The study will also explore the effect of the intervention on treatment-related variables including the dose of treatment received and response to neoadjuvant therapy.

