### Cardiopulmonary fitness and functional disability

Cardiopulmonary exercise testing will be used to assess VO_2_peak and functional disability. VO_2_peak, VT and ventilatory efficiency (Minute ventilation to carbon dioxide production slope [VE/VCO_2_ slope]) will be assessed using a continuous ramp protocol on an electronically braked upright cycle ergometer (Lode Excalibur Sport, Lode BV Medical Technology, Groningen, NL) with breath-by-breath expired gas analysis (Vyntus™ CPX, CareFusion, San Diego, CA) in accordance with published guidelines [48]. A flow meter and gas analyser calibration will be performed prior to each test in accordance with the manufacturer guidelines. Two minutes of resting data will be collected prior to the start of exercise, after which participants will undertake a one-minute warm-up at 10–25 W. The workload then increases at a continuous rate of 5–25 W/min until volitional fatigue or symptom limitation. The protocol will be individualised based on each participant’s self-reported physical activity levels, with the aim of reaching volitional exhaustion by 8–12 min. HR and rhythm will be monitored continuously throughout exercise using a 12-lead ECG (Vyntus™ CPX, CareFusion, San Diego, CA) and blood pressure (BP) will be measured every 2 min using an automated cuff (Tango® M2 ECG-gated Automated Blood Pressure Monitor, SunTech Medical Inc., Morrisville, NC). For the purposes of analysis, the test will be considered a peak effort if two of the following criteria are reached: 1) volitional exhaustion; 2) a respiratory exchange ratio > 1.1, and/or 3) > 85% of age-predicted maximal HR [48]. VO_2_peak is defined as the highest 30-s rolling average calculated from six consecutive 5-s VO_2_ epochs. Functional disability will be defined as a VO_2_peak ≤ 18.0 mL/kg/min ref. VT will be assessed using the V-slope method, and the relative proportion of VO_2_peak at which the VT occurs will be used as a measure of changes in submaximal exercise capacity. VE/VCO_2_ slope will be obtained from linear regression analysis of minute ventilation (VE) and expired carbon dioxide (VCO_2_) from the end of the warm-up to the VT [48]. HR and blood pressure (BP) recovery will also be assessed at 1, 2 and 4 min after the end of the test as markers of autonomic function.

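### The masking of outcome assessors to earlier results covers only pre-chemotherapy values, so the 4-month results fall outside it at the primary 12-month test (minor)

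*Protocol article*

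**What the plan says.** All statements are from the Protocol article.

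- *Randomisation and blinding*, on allocation: "Participants, care providers and outcome assessors will not be blinded to group allocation".
- Same section, on imaging: quantification of echocardiography and cardiac MRI "will be performed by researchers blinded to subject identity".
- Same section, on earlier results: "outcome assessors will be blinded to pre-chemotherapy values for all assessments".
- *Primary and secondary outcome measures*: the primary outcome is functional disability, a VO2peak threshold of 18.0 mL/kg/min, "measured via CPET at 12 months".
- *Cardiopulmonary fitness and functional disability*: the workload rises "until volitional fatigue or symptom limitation".
- *Phase 2, Aerobic ET*: tempo intensity is set around the ventilatory threshold "as measured from the follow-up CPET at the 4-month testing visit".
- *Study design*: baseline may be taken "no more than 2-weeks following the commencement of AC", because a baseline before the first dose is not always feasible.
- *Measurements*: session 1, which includes the exercise test, is planned before chemotherapy. Session 2 (strength, physical function, DXA) is aimed at the first two weeks of chemotherapy.

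**The concern.** The trial has three visits, and the primary outcome is read at the third. By masking assessors to earlier values, the protocol accepts that knowing them can colour a test. The rule is written around chemotherapy rather than around visits. At 4 months it covers the only preceding visit, late baselines apart. At 12 months it covers the first of two preceding visits and leaves out the more recent one.

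This matters most for the primary outcome. The exercise test depends on effort and on encouragement, and its result is then split at a fixed value. A tester who knows the arm and also a 4-month value close to 18 mL/kg/min knows which women could most easily change category. Strength and timed function tests are open to the same influence. The exercise arm's 4-month test has a working use that the controls' test does not, so some staff handle these results for one arm only.

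**Working it through.** The plan gives no figure for this point, so the main check sets the passages side by side.

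**Which earlier results are masked at the 12-month visit?**

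| Earlier result | Covered by the stated rule? |
|---|---|
| Baseline test done before chemotherapy | Yes |
| Baseline exercise test done after the first dose (exception allowed in *Study design*) | Not on a literal reading |
| Baseline strength, function, DXA done in the first two weeks of chemotherapy (*Measurements*) | Not on a literal reading |
| 4-month exercise test, strength, function and other in-person tests | No |
| Echo and cardiac MRI quantification, any visit | Separately masked to identity |

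No other section extends the rule to the 4-month visit. *Usual care group* calls the primary endpoint objective, but only in relation to patient expectancy and placebo effects. It does not address tester influence.

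**How few reclassifications matter?** This is for scale only and does not show that bias would occur. Take the plan's 45 per group and its 36% versus 12%, rounded to 16 and 5 women. Use an uncorrected chi-square as a stand-in for the planned mixed model:

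χ² = 90 × (ad − bc)² / (45 × 45 × row totals)

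- 16 v 5: 90 × (16×40 − 5×29)² / (2025 × 21 × 69) = 7.52, p = 0.006
- 16 v 7: 90 × (16×38 − 7×29)² / (2025 × 23 × 67) = 4.73, p = 0.030
- 16 v 8: 90 × (16×37 − 8×29)² / (2025 × 24 × 66) = 3.64, p = 0.057

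Three women changing category in one arm (5 to 8) would move the result across 5%.

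**Can the gap be given a size?** Simulation cannot isolate it. Assumptions, none of which is in the document: no true effect, 24% at or below 18 mL/kg/min in both arms, SD 4–5, correlation between 4 and 12 months 0.70–0.85, 45 per arm, two-sided pooled z-test, and an effort difference between arms of 0.5–1.0 mL/kg/min.

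| Effort shift applied to | Needs the 4-month value? | Rejection rate |
|---|---|---|
| Nobody | – | about 5.3% |
| Only women at 16–20 at 4 months (about 25–30%) | Yes | about 5.6–9.4% |
| All women | No, arm only | about 7–15% |

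The spurious difference in proportions is about 1–5 percentage points in the second row and about 3–8 in the third. The third row needs only knowledge of arm, which the protocol already concedes. The second row therefore describes an assumed arm-directed effort shift. It does not measure what knowing the 4-month value adds.

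**The case against.** **The real exposure is knowledge of arm.** This stands. It is disclosed, it is the larger route, and masking the 4-month results does not close it. A reader might infer from the 5.6–9.4% rejection rates that the gap inflates type I error to that level and that the fix removes the inflation. The document does not support this. The size and direction of the shift are assumed, and a shift that needs no 4-month value does more harm.

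**Pre-chemotherapy probably just means baseline.** This largely stands for the primary outcome, because *Measurements* plans the exercise test for the session before chemotherapy. A reader might infer that baseline VO2peak is commonly unmasked; only the allowed exceptions are affected. For session 2 tests the wording does not match the schedule. The 4-month point does not depend on this reading.

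**Nobody says that 12-month testers see 4-month results.** This stands as a limit. Phase 2 uses the heart-rate target at the ventilatory threshold. The article does not say that VO2peak values circulate or that prescribers run the 12-month tests, so a reader should not infer that exercise-arm values are known to testers.

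**The test is standardised.** This stands in part. VO2peak uses a fixed 30-second average, and peak effort needs two of three criteria, including respiratory exchange ratio and heart rate. Volitional exhaustion plus one other is enough, so some room for tester influence remains.

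**A journal article condenses, and access rules may sit elsewhere.** This stands for rostering and data-system access. It does not excuse a masking rule that the article does state and limits to one period.

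**Conclusion.** The point holds as a minor one. The stated safeguard is too narrow: it leaves out the most recent results before the primary test. The late-baseline part is mainly a matter of wording. It bears on strength, function and DXA, and on the exercise test only by exception. Echo and cardiac MRI quantification is outside the concern.

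The expected gain is a modest reduction in expectation bias, which cannot be quantified from the document. It rests on two assumptions: that 12-month testers could otherwise see 4-month results, and that knowing them influences how a test is run. Neither is documented, and neither is excluded.

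**What to change.** In *Randomisation and blinding*, replace the sentence on pre-chemotherapy values with:

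*Outcome assessors will be blinded to all results from earlier visits (baseline, whenever taken, and 4 months) for all assessments.*

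Add that 4-month results remain available to prescribing staff and for safety review. Where existing staffing allows, prescribers should not test their own participants at 12 months. This should be a preference and not a rule, since the article gives no staff numbers and strict separation might need resources it does not show.

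The cost is one sentence, a restricted view of earlier visits for testers, and possibly some rostering. The small downside is that testers cannot refer to the previous visit. The described exercise test does not need it, because its ramp is individualised from self-reported activity. The article reports that recruitment was continuing at submission, so on that status the change could still apply to 12-month tests not yet done.

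The change should not be presented as a remedy for unblinded assessment. Knowledge of arm should stay acknowledged as a limitation.

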### Intervention group

This is a multi-component periodised ET intervention designed to address the negative consequences of AC on cardiac, vascular, and skeletal muscle function. There will be three major phases to the program: Phase 1 - A 12-week structured, supervised exercise program conducted during AC; Phase 2 - A 14-week structured semi-supervised exercise program following AC; and Phase 3 - A 26-week step-down maintenance exercise program.

#### Phase 1 – structured exercise during AC (week 1–12)

The exercise training program conducted during AC will consist of 30–60 min of supervised, multi-modal exercise training performed three times per week. Sessions will use a combination of aerobic and progressive resistance training (PRT) and will be conducted at the Baker Heart and Diabetes Institute, the Deakin University Clinical Exercise Learning Centre, and participating health and fitness centres throughout metropolitan Melbourne. Sessions will be prescribed and overseen by an Accredited Exercise Physiologist (AEP), with all training supervised by appropriately trained AEPs and/or Exercise Scientists. A novel, non-linear step periodization model will be used due to its ability to adjust for fluctuations in each participant’s symptoms throughout their chemotherapy cycles whilst still allowing for adequate progression of training volume [46]. The model used in this study will involve a progressive increase in exercise volume of ~ 5–10% each week until the week immediately following each participant’s chemotherapy cycle. This week will be considered a ‘de-loading’ week where training intensity will be reduced by ~ 5%.

##### Aerobic ET

The aerobic component of the program will consist of both continuous steady state and interval-based training to provide varied forms physiological perturbation to the different components of the oxygen cascade that could be affected by chemotherapy [46]. Interval sessions will be performed on a cycle ergometer, whilst the continuous training will be performed on an upright cycle, treadmill and/or elliptical trainer based on participant preference. Exercise intensity will be individualised from each participant’s percentage of heart rate reserve (%HRR) at their ventilatory threshold (VT) measured during the baseline cardiopulmonary exercise test (CPET). Aerobic exercise intensity will be monitored by the 1–10 rating of perceived exertion (RPE) scale and wrist-worn heart rate (HR) monitors (Polar M200, Polar, Kempele, Finland), and these will be used to adjust the exercise workloads to account for day-to-day variation in participant health status throughout each chemotherapy cycle. The program will be broken into four training blocks based on participant’s scheduled chemotherapy in weeks 0, 3, 6 and 9 with progression of training volume outlined in Table 1. All sessions will include a 5-min aerobic warm up and cool-down. Following a one-week lead in period consisting of 3 sessions of 30-min at an intensity 10–15 beats/min below the VT, participants will complete two steady state aerobic sessions and one vigorous to high intensity interval session per week for the remaining 11 weeks, with progressive increases in exercise duration and/or intensity as outlined in Table 1. Interval sessions will begin in week 2, and consist of four work intervals of 2–4 min progressing from the %HRR corresponding to VT and progressing to 85–95% HR_peak_, interspersed with 3-min of cycling at a light intensity. The target intensity of the continuous and interval training will be reduced by ~ 5% in week 3, 6 and 9 to account for the increased symptom burden of each chemotherapy cycle.

**Table 1 Tab1:** Progression of the 12-month multi-modal exercise training program

Phase	Cycle	Weeks	Session Type	Frequency (per week)	Duration/Dose	Intensity^**a**^
Phase 1 Supervised Exercise During AC	1	1–3	Steady State & Resistance Training	2	SS: 30 mins RT: 1–2 sets × 12–15 reps	SS: 10–20 b/min below %HRR at VT RT: 60–70% 1RM
			Interval Training	1	4 × 2 mins^b^	%HRR at VT ± 5 b/min
	2	4–6	Steady State & Resistance Training	2	SS: 30 mins RT: 2 sets × 12–15 reps	SS: 10–15 b/min below %HRR at VT RT: 60–70% 1RM
			Interval Training	1	4 × 3 mins^b^	%HRR at VT ± 5 b/min
	3	7–9	Steady State & Resistance Training	2	SS: 30–35 min RT: 2 sets × 18–12 reps	SS: 5–10 b/min below %HRR at VT RT: 70–85% 1RM
			Interval Training	1	4 × 3 mins^b^	85–95% HR_peak_
	4	10–12	Steady State & Resistance Training	2	SS: 35–40 min RT: 2 sets × 8–12 reps	SS: 5–10 b/min below %HRR at VT RT: 70–85% 1RM
			Interval Training	1	4 × 4 mins^b^	85–95% HR_peak_
Phase 2 Semi-supervised Exercise Following AC	1	13,15,17	Endurance Training	1	40–50 min	15–20 b/min below %HRR at VT
			Tempo Training & Resistance Training	2	TT: 35 mins RT: 2 sets × 8–12 reps	TT: 5–10 b/min below %HRR at VT RT: 70–85% 1RM
			Interval Training	1	4 × 4 mins^b^	85–95% HR_peak_
		14,16	Tempo Training	1	35 mins	5–10 b/min below %HRR at VT
			Interval Training & Resistance Training	2	IT: 4 × 4 mins^b^ RT: 2 sets × 8–12 reps	IT: 85–95% HR_peak_ RT: 70–85% 1RM
			Recovery Session	1	30 mins	25–30 b/min below %HRR at VT
	2	18,20,22	Tempo Training	1	35 mins	0–5 b/min below %HRR at VT
			Interval Training & Resistance Training	2	IT: 4 × 4 mins^b^ RT: 2 sets × 8–12 reps	IT: 85–95% HR_peak_ RT: 70–85% 1RM
			Recovery Session	1	30 mins	20–25 b/min below %HRR at VT
		19,21	Endurance Training	1	50–60 min	15–20 b/min below %HRR at VT
			Tempo Training & Resistance Training	2	TT: 35 mins RT: 2 sets × 8–12 reps	TT: %HRR at VT ± 5 b/min RT: 2 sets × 8–12 reps
			Interval Training	1	4 × 4 mins^b^	85–95% HR_peak_
	3	23,25	Endurance Training	1	60 mins	10–20 b/min below %HRR at VT
			Tempo Training & Resistance Training	2	TT: 35 mins RT: 2 sets × 8–12 reps	TT: %HRR at VT ± 10 b/min RT: 70–85% 1RM
			Interval Training	1	4 × 4 mins^b^	85–95% HR_peak_
		24,26	Tempo Training	1	35 mins	%HRR at VT ± 10 b/min
			Interval Training & Resistance Training	2	IT: 4 × 4 mins^b^ RT: 2 sets × 8–12 reps	IT: 85–95% HR_peak_ RT: 70–85% 1RM
			Recovery Session	1	30 mins	20–25 b/min below %HRR at VT
Phase 3 Maintenance	n/a	27–52	Endurance Training	1	60 mins	10–20 b/min below %HRR at VT
			Tempo Training & Resistance Training	2	TT: 35 mins RT: 2 sets × 8–12 reps	TT: %HRR at VT ± 10 b/min RT: 2 sets × 8–12 reps
			Interval Training	1	4 × 4 mins^b^	85–95% HR_peak_

*Abbreviations*: *%HRR* Percentage of heart rate reserve, *1RM* One repetition max, *HR*_*peak*_ Heart rate peak, *IT* Interval training, *RT* Resistance training, *TT* Tempo training, *VT* Ventilatory threshold

^a^Intensity reduced by 5% from values reported in table during the week following chemotherapy administration

^b^Only duration for work phase of intervals is reported – duration for recovery phase was 3 min of light-intensity cycling

##### Progressive resistance training

For two of the three weekly sessions, participants will also complete six compound PRT exercises (three upper body, three lower body) with a primary focus on improving muscle strength and muscle mass. The PRT exercises will be performed for 1–2 sets of 8–15 repetitions depending on the training cycle (outlined in Table 1). Examples of the exercises to be incorporated in the program include leg press, squats, lunges, step-ups, chest press, overhead press, seated row, and latissimus dorsi pulldown. During the first 6-weeks of the program, participants will perform 1–2 sets of 12–15 repetitions at 60–70% of their one repetition maximum (1RM) strength with 1 min of rest in between each set. During the weeks 7–12 of the program, participants will perform 2 sets of 8–12 repetitions at 70–85% of their 1RM with 1–2 min rest in-between each set. All participants will be instructed to lift and lower the weight in a slow- and controlled manner. Resistance exercises performed in weeks 1–6 will be changed or slightly modified during weeks 7–12 to provide training variety, and progression.

